### Strategies to improve adherence to interventions {11c}

This study required the investigators to provide data on whether they performed the treatment assigned to them. Information on the type, quantity, and temperature of the solutions used for irrigation is to be collected.

### Relevant concomitant care permitted or prohibited during the trial {11d}

Reoperation at a stage that does not meet the criteria for reoperation is prohibited. All other medical treatments are permitted.

### Provisions for posttrial care {30}

This study will implement and collect data on treatments accepted by national insurance in Japan. Therefore, it is not compensable to those likely to suffer harm from trial participation, as per clinical research insurance, and is handled the same as normal medical treatment.

### Outcomes {12}

#### Assessment items

The demographic information collected includes age, sex, medical history, lifestyle history, and traumatic episodes that may have contributed to the condition. Patients’ living situations, whether at home, in a hospital, rehabilitation center, or nursing home, are to be recorded as well.

Neurological status is to be assessed using the modified Rankin Scale (mRS), Glasgow Coma Scale (GCS), Markwalder classification, and any existing neurological symptoms. The modified Rankin Scale (mRS) was developed to evaluate the severity of stroke outcomes. However, its application extends to clinical assessments of CSDH [30–32]. This scale ranges from 0, denoting the absence of symptoms, to 6, which signifies death (Table 2). GCS is used to objectively express the degree of impairment of all types of consciousness in terms of the three aspects of eye-opening, motor, and verbal reactions (Table 3). The Markwalder classification divides the severity of symptoms of CSDH into 0–4 [33] (Table 4). The scores on these scale at will be determined by physicians who were trained to obtain them.

**Table 2 Tab2:** Modified Rankin Scale (mRS)

Score	Description
0	No symptoms
1	No significant disability: Despite symptoms, able to carry out all usual duties and activities
2	Slight disability: Unable to perform all previous activities but able to look after own affairs without assistance
3	Moderate disability: Requiring some help but able to walk without assistance
4	Moderately severe disability: Unable to walk without assistance and unable to attend to own bodily needs without assistance
5	Severe disability: Bedridden, incontinent, and requiring constant nursing care and attention
6	Death

**Table 3 Tab3:** Glasgow Coma Scale (GCS)

Eye opening		Verbal response		Motor response	
Score	Description	Score	Description	Score	Description
4	Eyes open spontaneously	5	Orientated	6	Obeys commands
3	Eye opening to sound	4	Confused	5	Localizing pain
2	Eye opening to pain	3	Inappropriate words	4	Withdrawal from pain
1	No eye opening	2	Incomprehensible sounds	3	Abnormal flexion to pain
		1	No verbal response	2	Abnormal extension to pain
				1	No motor response

**Table 4 Tab4:** Markwalder classification

Grade	Description
0	Patient neurologically normal
1	Patient alert and oriented; mild symptoms such as headache; absent or mild neurological deficit, such as reflex asymmetry
2	Patient drowsy or disoriented with variable neurological deficit, such as hemiparesis
3	Patient stuporous but responding appropriately to noxious stimuli; severe focal signs, such as hemiplegia
4	Patient comatose with absent motor responses to painful stimuli; decerebrate or decorticate posturing

Based on cranial CT imaging, the architecture of the CSDH, volume of the hematoma, and midline shift will be assessed. The hematoma architecture is classified into four distinct types according to the framework established by Nagaguchi et al.: homogeneous, laminar, separated, and trabecular [21]. The homogeneous type is characterized by a uniform density that varies from low to high. In contrast, the laminar type, a variation of the homogeneous, is distinguished by a thin, high-density layer along the inner membrane. The separated type comprises two distinct density zones with a clear demarcation, typically a lower density component located above a higher density component. The ‘gradation’ subtype with ambiguous boundaries is also included in the separated type. Finally, the ‘trabecular’ type presents inhomogeneous contents and a high-density septum running between the inner and outer membrane on a low-density to isodense background. The hematoma volume was calculated from the maximum width (A), length (B), and height (C) using the formula A × B × C/2 [34]. The midline shift is measured as the deviation of the midline at the slice where the foramen of Monroe can be seen on the CT axial image.

Medications are divided into those that may impact the recurrence of CSDH, such as antithrombotic agents, steroids, statins, and goreisan, and those that do not. Surgical details included surgeon experience, surgery duration, irrigation fluid volume, direction of the inserted drain, and temperature of the irrigation fluid (room temperature or equivalent to body temperature).

Adverse events are to be documented when they occur. Personally identifiable information, such as name and address, will not be recorded on REDCap® data to ensure the anonymity of individual participants.

### Primary endpoint

The primary endpoint is the proportion of patients who meet the criteria for ipsilateral reoperation within 6 months of surgery.

### Criteria for reoperation

Reoperation is indicated when the following two criteria are simultaneously fulfilled:(i)Neurological symptoms are present that are considered to be caused by ipsilateral CSDH.(ii)The hematoma has increased in size compared to immediately after surgery and compressed the brain parenchyma in CT scans.

### Secondary endpoints

The proportion of reoperations within 6 monthsThe proportion of reoperation stratified by preoperative hematoma architecture determined by CT scansModified Rankin Scale, Glasgow Coma Scale, and Markwalder classification at 6 monthsMortality at 6 monthsComplications related to the operationLength of hospital stay from surgery to discharge (including time spent in a rehabilitation unit)Duration of the surgical procedure

### Participant timeline {13}

Data will be recorded in Research Electronic Data Capture (REDCap®) preoperatively, intraoperatively, within 72 h (postoperatively), at hospital admission, 4–6 weeks (postoperatively), and 6 months (postoperatively) (Fig. 1).

**Fig. 1 Fig1:**
[figure not shown]
Checklist table. †Timepoint =  − *t*_1_, baseline (before surgery); 0, allocation; *t*_1_, surgery; *t*_2_, within 72 h after surgery; *t*_3_, at admission; *t*_4_, 4–6 weeks after surgery; *t*_5_, 6 months after surgery. *If reoperation has not been performed at 6 months postoperatively, imaging studies must be performed in patients with worsening neurological symptoms. Radiological imaging is not always necessary if the patient’s symptoms are stable

### Sample size {14}

The present study aimed to recruit 1186 cases, with 593 patients allocated to each group. The target number of cases was determined based on a previous meta-analysis that examined the efficacy of irrigation for CSDH. A meta-analysis reports a recurrence proportion of 8.06% (38/471) in the irrigation group and 13.05% (59/452) in the non-irrigation group; however, this difference was not statistically significant [17]. The 95% confidence intervals were 5.8–10.9% for the irrigation group and 10.1–16.5% for the non-irrigation group. To account for the differences in outcome measures between the prior and present studies, we set the proportions of patients meeting the criteria for ipsilateral reoperation at 7% for the irrigation group and 12% for the non-irrigation group. Using *α* = 0.05 and *β* = 0.20 and accounting for a 10% dropout proportion, a total of 1186 cases, with 593 cases in each group, have been calculated to be necessary for the current study. In determining the sample size, the sample size calculation tool for 2 × 2 contingency tables by Kazuhiko Nagashima was used [35] (https://nshi.jp/contents/js/twofreq/).

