## Assignment of interventions: allocation

### Sequence generation {16a}

Randomization was performed using a minimization method of balancing age (69 years or younger vs. 70 years or older), hematoma architecture on CT scans (homogeneous, stratified, isolated, and trabecular), the presence of antiplatelet therapy, preoperative GCS score (13 or lower vs. 14 or higher), and institution at baseline in a 1:1 ratio. If there is a small contralateral hematoma, only the hematoma architecture is considered when performing surgery.

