## Statistical methods

### Statistical methods for primary and secondary outcomes {20a}

A statistician blinded to the treatment assignments will perform the analysis. For the primary endpoint, we will adhere to the intention-to-treat (ITT) principle; all patients who have been randomized and underwent surgery will be analyzed according to the group they were allocated to, irrespective of the treatment they received. When outcomes are missing for these patients, they will be treated as not having met the criteria for reoperation. The comparison for this endpoint between the two groups will be made using Fisher’s exact test. As a secondary analysis, the odds ratio estimates and their 95% confidence intervals will be calculated for the primary endpoint and secondary endpoints of the proportion of reoperations, the proportion of deaths, and the proportion of surgery-related complications. For the secondary endpoints of mRS, change in GCS, time from surgery to discharge, and operative time, the two groups will be compared by calculating the mean difference between the groups and its 95% confidence interval. 95% confidence intervals will be calculated using the Clopper-Pearson and bootstrap methods, respectively.

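### The stated 80% power at 10% dropout matches an uncorrected chi-square test; under the planned Fisher's exact test it is about 77%

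*Protocol article*

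**What the plan says.** The section Sample size {14} gives the design inputs: "Using *α* = 0.05 and *β* = 0.20", and reoperation-criteria proportions of "7% for the irrigation group and 12% for the non-irrigation group". It concludes that, "accounting for a 10% dropout proportion, a total of 1186 cases, with 593 cases in each group, have been calculated to be necessary". The source of the calculation is given only as "the sample size calculation tool for 2 × 2 contingency tables". Neither the test nor the sidedness is stated.

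The section Statistical methods for primary and secondary outcomes {20a} then fixes the primary test: "The comparison for this endpoint between the two groups will be made using" Fisher's exact test. The same section analyses everyone who was randomized and had surgery in the allocated group, and counts a missing primary outcome as not meeting the reoperation criteria.

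**The concern.** A power statement belongs to a particular test. Fisher's exact test is conservative for a 2 × 2 table of this size: its true type I error lies below the nominal 5%, so it needs more patients than the uncorrected chi-square for the same power. If the number of patients came from the chi-square formula and the analysis uses Fisher's test, the β quoted in the sample size section is not the β of the planned analysis at the planned dropout. The protocol plans no interim analysis, so no later step is scheduled at which the figure would be revisited.

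**Working it through.** **Inputs.** From Sample size {14}: p₁ = 0.07, p₂ = 0.12, α = 0.05, power 0.80, dropout 10%, 593 per arm. From Sequence generation {16a}: 1:1 allocation. From Statistical methods {20a}: Fisher's exact test, with missing outcomes set to non-event. Two-sided α is assumed, because the one-sided size does not reproduce the figure (below).

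**Step 1: reproduce 593.** For the two-sided chi-square with pooled variance and no continuity correction, with p̄ = 0.095:

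n = [1.960·√(2·0.095·0.905) + 0.842·√(0.07·0.93 + 0.12·0.88)]² / 0.05²

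= [1.960·0.4147 + 0.842·0.4132]² / 0.0025 = 538.7, so 539 per arm.

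539 × 1.10 = 592.9, so 593 per arm and 1186 in total. This is an exact match.

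The alternatives do not give 593:

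| Sizing method | Per arm before loss | × 1.10 | ÷ 0.90 |
|---|---|---|---|
| Chi-square, pooled, uncorrected | 539 | **593** | 599 |
| Chi-square, unpooled | 536 | 590 | 596 |
| Arcsine | 531 | 584 | 590 |
| Continuity-corrected | 578 | 636 | 643 |
| Fisher, exact enumeration | 572 | 630 | 636 |
| One-sided, uncorrected | 425 | 468 | 473 |

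**Step 2: power of the planned test.** For each pair of counts (x₁, x₂) from two binomials, the two-sided Fisher p-value was computed from the hypergeometric distribution, and the joint probabilities of all pairs with p ≤ 0.05 were summed. The uncorrected chi-square was enumerated over the same tables.

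Loss can enter in two ways. Removing 10% leaves 593 × 0.9 = 533.7, or 534 per arm. Under the rule in {20a}, 593 stay in and the missing become non-events. If all of them would otherwise have kept the design event rates, the proportions become 0.9 × 7% = 6.3% and 0.9 × 12% = 10.8%.

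| Scenario | Fisher | Uncorrected chi-square |
|---|---|---|
| 593 per arm, no loss | 81.6% | 84.0% |
| 534 per arm (10% removed) | 77.1% | 80.2% |
| 593 per arm, 6.3% vs 10.8% | 76.7% | 79.5% |

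Fisher's test first reaches 80% at 572 evaluable per arm (571 gives 79.93%, 572 gives 80.01%).

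**Step 3: how much loss it takes.** With missing outcomes set to non-event at 593 per arm, Fisher's power is 80.7% at 2% missing, 80.2% at 3%, just under 80% at 4%, and 79.3% at 5%.

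**Step 4: does the chi-square hold its level?** By enumeration at 534 per arm under equal rates of 7%, 9.5% and 12%, its type I error is 4.96% to 5.02%. Fisher's is 3.8% to 4.0%. The lost power is therefore the price of unused α, not of protection that the chi-square lacks here.

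**The case against.** Several points on the other side stand.

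The chi-square basis is an inference. The protocol names no test and the settings of the tool are not shown. The exact match makes the inference strong, but the power figures do not depend on it: they follow from 593, the stated rates and the stated test.

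The shortfall depends on loss. With none, Fisher's test exceeds 80%, and the plan to check 6-month status by telephone when a visit is missed works against loss. Still, 10% is the protocol's own planning figure, and the power statement is tied to it.

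The 76.7% is a worst case. Data are also recorded within 72 h and at 4–6 weeks, so events seen before a patient is lost would still count.

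Three points are small beside the uncertainty in the event rates. At 534 per arm, moving the non-irrigation rate from 12% to 12.25% raises Fisher's power to 80.8%, and at the meta-analysis rates (8.06% and 13.05%) it is about 73%. That argues for modest weight. It does not make the stated figure correct under its own inputs.

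A reader might also infer that the dropout inflation is a second material error, because 539 ÷ 0.90 is 599 rather than 593. The figures do not support this. The chi-square still has 80.2% exact power at 534 per arm, so the six patients per arm make no practical difference and the target need not change to 599.

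**Conclusion.** The sample size statement and the primary test are not aligned. At the stated rates and the stated 10% dropout, the planned Fisher's exact test has about 77% power, so β is about 0.23 rather than 0.20. With no loss the power is 81.6%. This rests on a two-sided α of 0.05, the design rates of 7% and 12%, and equal loss in both arms.

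A reader might go further and conclude that the design cannot reach 80% power, that the trial must enrol 636 per arm (572 ÷ 0.9), or that the primary test is unsound. None of these follows. The shortfall appears only once loss reaches roughly 4%. It can be recovered through the choice of test without more patients. Fisher's test is valid and conservative, so there is no inflated error rate and no bias from this source. The point is of moderate severity: a figure that should be corrected, not a flaw that undermines the trial.

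**What to change.** One of two changes is enough.

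1. Keep Fisher's exact test and correct Sample size {14}: name the test used for sizing, and state that under Fisher's test 593 per arm gives about 77% power at 10% dropout and about 82% at none. This costs one sentence and leaves the analysis unchanged.

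2. Make the uncorrected chi-square the primary test in {20a} and keep Fisher's test as a sensitivity analysis. Power at 10% loss is then about 80% (80.2% with losses removed, 79.5% in the worst case), with a true size of about 5%. This is more than a wording change. Enrolment began in January 2023 and the trial is not blinded, so altering the primary test could look driven by results. It should be made by amendment or in the SAP that the protocol promises before data lock, and dated before anyone has seen outcomes by arm. The large-sample approximation is not a concern: about 113 events are expected at full enrolment (593 × 0.07 + 593 × 0.12 = 112.7).

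Neither option needs more patients or a change to the target of 1186.

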### Recruitment {15}

All CSDH patients who meet the eligibility criteria are eligible to participate. If the doctors at each site cannot immediately determine whether a patient is eligible to participate, the Nagoya University research team will respond to queries.

## Assignment of interventions: allocation

### Sequence generation {16a}

Randomization was performed using a minimization method of balancing age (69 years or younger vs. 70 years or older), hematoma architecture on CT scans (homogeneous, stratified, isolated, and trabecular), the presence of antiplatelet therapy, preoperative GCS score (13 or lower vs. 14 or higher), and institution at baseline in a 1:1 ratio. If there is a small contralateral hematoma, only the hematoma architecture is considered when performing surgery.

### Concealment mechanism {16b}

Clinical information required for the minimization method would be inserted into a web-based registration system for allocation. This process will be performed before surgery, and no registrations will be accepted thereafter.

### Implementation {16c}

Registration and randomization of patients will be performed by the physician at each participating facility when the decision for surgery has been made and consent from the patient or proxy has been obtained. The physician at each site will perform the surgery according to the method allocated in the web system.

## Assignment of interventions: blinding

### Who will be blinded {17a}

Given the nature of surgical intervention, it is impossible to blind the medical staff involved. Furthermore, since the primary outcome measure is meeting the criteria for reoperation, blinding the participants would be meaningless. Therefore, from the perspective of protecting participants’ rights, participant blinding will not be implemented either.

### Procedure for unblinding if needed {17b}

Blinding will not be performed in this study.

## Data collection and management

### Plans for assessment and collection of outcomes {18a}

All data will be collected and entered online by investigators at each site using REDCap®. The physician at each site will document medical records based on the data collection items, and these records will be the primary source for input into REDCap®. The results will be verified by the Nagoya University research team during the study. If data has not been entered, an email will be sent to the investigators at each site to encourage them to enter the data.

### Plans to promote participant retention and complete follow-up {18b}

If the patient does not attend according to the established schedule, the study investigator will contact the patient or family member to ask about the situation and whether the investigator can provide assistance to avoid future missed sessions. If the patient cannot visit for the 6-month postoperative assessment of the primary outcome, the status would be checked telephonically.

### Data management {19}

The REDCap online database serves as a platform for gathering and storing data in an academic context, ensuring password-protected access for authorized researchers. Physicians at each site can only enter and review data for their own site. Only the Nagoya University research team has access to data from all sites. This database incorporates mandatory data entry fields to minimize missing data. It also offers features such as range checking of data values and question branching. The gathered data will be handled and stored in compliance with the management plan established according to Nagoya University’s Research Data Management Policy.

### Confidentiality {27}

The forms used to code the patients are stored at each site in a locked cabinet accessible only to the investigators and administrators responsible for the study. Individual patient-identifiable information will not be entered into the REDCap®.

### Plans for collection, laboratory evaluation, and storage of biological specimens for genetic or molecular analysis in this trial/future use {33}

No additional biological samples are collected from participants other than those taken as part of routine medical care.

## Statistical methods

### Statistical methods for primary and secondary outcomes {20a}

A statistician blinded to the treatment assignments will perform the analysis. For the primary endpoint, we will adhere to the intention-to-treat (ITT) principle; all patients who have been randomized and underwent surgery will be analyzed according to the group they were allocated to, irrespective of the treatment they received. When outcomes are missing for these patients, they will be treated as not having met the criteria for reoperation. The comparison for this endpoint between the two groups will be made using Fisher’s exact test. As a secondary analysis, the odds ratio estimates and their 95% confidence intervals will be calculated for the primary endpoint and secondary endpoints of the proportion of reoperations, the proportion of deaths, and the proportion of surgery-related complications. For the secondary endpoints of mRS, change in GCS, time from surgery to discharge, and operative time, the two groups will be compared by calculating the mean difference between the groups and its 95% confidence interval. 95% confidence intervals will be calculated using the Clopper-Pearson and bootstrap methods, respectively.

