### Criteria for discontinuing or modifying allocated interventions {11b}

After randomization, patients who wish to change their assigned surgical procedure can request an intervention change and withdraw from the trial. Patients do not have to provide the reason for withdrawal. If the surgeon intentionally or unintentionally administers a treatment different from the assigned group after randomization, the case will be excluded from the analysis, and crossover of participants is not permitted. This approach ensures the integrity of the trial and respects patient autonomy.

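### The primary analysis is called intention-to-treat but includes only randomised patients who went on to surgery, so it is a modified ITT set; the likely bias is small and the correction is cheap

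*Protocol article*

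**What the plan says.** All references are to the protocol article.

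- **Label.** Statistical methods {20a}: "For the primary endpoint, we will adhere to the intention-to-treat (ITT) principle".
- **Set.** The same sentence goes on: "all patients who have been randomized and underwent surgery will be analyzed according to the group they were allocated to". It adds that the treatment actually received does not matter.
- **Missing outcomes.** The next sentence reads: "When outcomes are missing for these patients, they will be treated as not having met the criteria for reoperation". The patients meant are those just defined, so a randomised patient without surgery is outside this rule too.
- **Timing.** Concealment mechanism {16b} says of registration and allocation: "This process will be performed before surgery, and no registrations will be accepted thereafter". Implementation {16c} places randomisation at the point "when the decision for surgery has been made and consent from the patient or proxy has been obtained", and the site physician then operates by the method allocated.
- **Blinding.** Section {17a} provides none, for staff or participants.
- **Exit after allocation.** Section {11b} lets a patient who wants a different procedure from the one assigned ask for a change and leave the trial. It adds: "Patients do not have to provide the reason for withdrawal". The same section removes from the analysis any case given the other arm's treatment.
- **Endpoint.** The primary endpoint is counted over 6 months from surgery, and the second reoperation criterion compares haematoma size with its size just after surgery.

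**The concern.** An ITT comparison keeps the groups as randomisation formed them. Requiring that surgery took place adds a condition that is met, or not, after allocation. Such a condition does no harm when starting treatment cannot depend on knowing the assignment. Nothing in this design guarantees that: the physician who registers the patient sees the arm before operating, and section {11b} itself foresees patients leaving because of the procedure assigned to them.

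If cancellation, postponement or withdrawal before surgery differed by arm and were related to prognosis, the analysed groups would no longer be those that the minimisation produced. The trial report would then carry a label that its primary analysis does not meet.

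**Working it through.** **1. The plan's own figure.** Inputs from Sample size {14}: 7% and 12%, α = 0.05 (taken as two-sided), power 80%, 10% dropout. With the pooled-variance formula and no continuity correction:

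n = [1.960·√(2 × 0.095 × 0.905) + 0.842·√(0.07 × 0.93 + 0.12 × 0.88)]² / 0.05² = 539 per arm.

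539 × 1.1 = 593 per arm, 1186 in total. The stated figure reproduces, and nothing in this point alters it.

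**2. Who falls outside the set.**

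| Patient after randomisation | Set in {20a} | Missing-outcome rule in {20a} |
|---|---|---|
| Operated on, outcome known | included | not needed |
| Operated on, outcome missing | included | counted as no event |
| Never operated on | excluded | does not apply |

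The last row separates this set from an all-randomised set. Analysing patients regardless of treatment received deals with crossover among operated patients. It does not bring back those who had no operation.

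**3. Size of a one-arm loss.** Let an arm have risk 12% over all its randomised patients. Suppose a fraction f is not operated on and has risk r. The remaining patients then have risk (0.12 − f·r)/(1 − f), so the shift is f(0.12 − r)/(1 − f). The documents give no value for f or r; all values below are assumptions. The 36% is three times the planning rate, chosen as an extreme.

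| f (patients of 593) | r = 0 | r = 24% | r = 36% |
|---|---|---|---|
| 2% (about 12) | 0.0024/0.98 = +0.24 points | −0.0024/0.98 = −0.24 | −0.0048/0.98 = −0.49 |
| 5% (about 30) | 0.0060/0.95 = +0.63 points | −0.0060/0.95 = −0.63 | −0.0120/0.95 = −1.26 |

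The planned difference is 12 − 7 = 5 points.

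**4. Effect on the planned test (two-sided Fisher's exact).**

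- At about the planned rates, 42 v 71 events of 593 each give p = 0.005. With 48 v 71, dropping 12 event-free patients from the irrigation arm still gives p = 0.042.
- Near the threshold a few patients can decide the result. With 50 v 71, p = 0.055; dropping 6 event-free patients (1%) from the non-irrigation arm gives 0.044. With 49 v 71, p = 0.043; dropping 12 (2%) from the irrigation arm gives 0.054. These counts were picked to lie at the threshold.
- With both arms truly at 12%, losing event-free patients from one arm only moves the type I error from 4.1% to about 4.5% (1% lost), 4.7% (2%) and 5.6% (5%).

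**5. Cost of keeping everyone.** If 1% of each arm were unoperated, with the same risk in both arms, a 5.0-point effect would become 0.99 × 5.0 = 4.95 points.

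**The case against.** The case for the present set has four parts.

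- **Endpoint.** It is tied to surgery. A patient never operated on has no surgery date, no postoperative scan for comparison and no possible reoperation, so there is no outcome to enter without a new rule. This stands: an all-randomised set needs an explicit time origin and outcome value, not only a change in the definition of the set.
- **Rarity.** Arm-dependent non-operation should be uncommon. Patients have symptomatic disease needing evacuation, consent to surgery first, and are randomised only once it is decided. Both arms receive a burr hole and a drain. Someone who dislikes the allocation is more likely to have the other procedure than none. This stands too, and it is why the likely bias is small.
- **Withdrawal.** Patients who leave before surgery may not be followable, and scoring them event-free would be another untested assumption. This also stands, and is why a sensitivity analysis should score them both ways.
- **Openness.** The set is stated plainly, so nobody is misled about who is analysed. This stands only in part: the stated principle and the stated set still disagree.

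A reader might infer that patients are known to learn their arm before surgery. The document does not say so. Section {17a} says only that they are not blinded, and section {11b} implies knowledge by allowing a wish to change the assigned procedure. The surgeon's knowledge follows directly from {16c} and is enough for the argument.

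**Conclusion.** The primary set is modified ITT under an ITT label, and its missing-outcome rule leaves unoperated patients out. That much rests on the text alone.

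The numerical consequence is probably small. Under assumed one-arm losses of 2% to 5%, the affected arm moves by about +0.2 to +0.6 points if those lost are event-free, and by −0.5 to −1.3 points if they carry an assumed 36% risk. Bias arises only if non-operation differs by arm and is related to prognosis. The documents supply no rate for either.

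A reader might infer that the primary comparison will be materially biased or that the sample size is wrong. The documents support neither: the sample size reproduces, and the routes to arm-dependent non-operation are narrow. The change is worth making because it is cheap and restores a property that the trial claims.

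The conflict between {20a}, which ignores treatment received, and {11b}, which drops wrongly treated cases, concerns operated patients and is the larger problem in this area. It should be settled in the same edit.

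**What to change.** Amend Statistical methods {20a} in one of two ways.

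1. Define the primary set as all randomised patients in their allocated arm. Add a rule for those never operated on: time counted from randomisation, and a stated outcome value, because the endpoint and reoperation criteria are defined only after surgery.
2. Keep the present set, call it modified ITT, and prespecify an all-randomised sensitivity analysis that scores unoperated patients once as event-free and once as events.

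In either case, report the number of patients without surgery and the reasons, by arm. Withdrawal needs no reason, so some will be recorded as not given. Also reconcile {20a} with the exclusion of wrongly treated cases in {11b}, so that one rule governs the primary analysis.

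The cost is a short amendment carried into the SAP, a little extra analysis and, under the first option, 6-month follow-up of what should be few patients. The statistical price is slight dilution: about 0.05 points if 1% of each arm is unoperated.
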